## Method

### Study design

This protocol outlines a quasi-experimental Hybrid Design Type-3 effectiveness implementation study.

### PRITAH- intervention

The Prevention and Reduction of Involuntary Treatment At Home (PRITAH) intervention aims to support healthcare professionals and informal caregivers with knowledge and tools that can help prevent and reduce involuntary treatment at home. The intervention consists of four key elements: (1) implementation of policy in homecare organizations aimed to discourage the use of involuntary treatment; (2) a plenary kick-off meeting and three workshops for CMDs including practical assignments and case studies; (3) on-the-job coaching and consultation by a specially trained case manager in the field of dementia or common care nurse; and (4) availability and utilization of alternative interventions for involuntary treatment alternatives to prevent involuntary treatment use [28]. A summary of the four key elements is presented in Table 1.

**Table 1 Tab1:** Key elements of the PRITAH- intervention

Policy	The policy emphasizes that the organization will no longer apply involuntary treatment. It also sets clear conditions, such as raising awareness, adopting a multidisciplinary approach, maintaining communication with caregivers, and using alternatives. The policy is written and introduced to care professionals through the organization’s management.
***Education (2.5 h per workshop)***	Kick-off meeting - A general introduction to the PRITAH intervention and an overview of the three PRITAH- workshops by the research team. Workshop 1: increasing knowledge and awareness - Dilemmas about involuntary treatment, explaining the home care organization’s policy on its use, and providing an overview of current literature on its prevalence, risk factors, and consequences. Workshop 2: methodological approaches & alternatives - Methodological approach for situations involving involuntary treatment and exploring alternatives to prevent or reduce its use. Workshop 3: communication with stakeholders - Communication between caregivers, informal caregivers, and PLWD about involuntary treatment use, and using case studies to practice communication and for finding possible alternatives to involuntary treatment. Practical assignments between each workshop All workshops are given by specially trained nurses or case managers in the field of dementia care.
***Consultation and on-the-job coaching***	Consultation - Offering 30-minute consultation sessions, such as during team meetings, and providing guidance on preventing involuntary treatment in daily practice. On-the-job coaching - Available for questions and coaching in daily practice, with the coach serving as the primary point of contact for inquiries. *The trainers of the workshops will serve as a coach. *
***Alternatives***	Alternatives for involuntary treatment use will be discussed during the workshops and consultation sessions. A comprehensive list with alternatives will be provided to the participants. *The organizations are responsible for the availability of alternatives.*

### Study setting and sample

#### Setting

In the Netherlands, when informal caregivers are no longer able to care for PLWD or meet their needs or wishes, professional support from general practitioners and homecare is provided. Homecare organizations in the Netherlands are organized in small districts, each managed by a team of nurses. Within each district team, a district nurse is responsible for planning, coordinating, delivering, and assessing care within a PLWD home environment [36]. Depending on the support needed by the PLWD, other members of the district team may include common care nurses, vocationally trained nurses, nursing assistants, and domestic workers. Additional to usual homecare practices, CMDs play an important role in the care for PLWD at home. They are specially trained nurses or social workers involved in the care process once a diagnosis of dementia has been made. Their primary role is to act as a bridge between professionals and organizations, streamlining care delivery for PLWD and enhancing communication among stakeholders. CMDs are often perceived as key sources of support and guidance, remaining closely involved with PLWD and their caregivers from diagnosis through to institutionalization or end of life [37].

#### Sample

The study will take place within the region of South Limburg in the Netherlands, home to a population of 402,700 individuals [38]. Of this population, 27.4% are 65 years or older and 2.2% (8,660 individuals) are diagnosed with dementia [39, 40]. In 2020, CMDs supported approximately 33–41% (i.e. 2,858 to 3,551) of the people living with dementia at home in the region [41]. In this large region, 88 CMDs employed by four professional homecare organizations are responsible for the dementia care in this region. Each CMD manages a caseload of approximately 55 clients (i.e. PLWD) in a fulltime position or proportionally in a part time position. All 88 CMDs working in the region of South Limburg in the Netherlands are invited to participate in the study on the implementation of the PRITAH-intervention. The CMDs are employed across four organizations in two regions and are each assigned to a specific city district or village within that region. To avoid contamination, all CMDs within the same district or village are grouped together, resulting in multiple clusters. These clusters are then allocated to either the intervention or the control condition, ensuring that CMDs within a given cluster did not interact across conditions. The CMDs in the intervention group receive training in batches of 10 to 14 people, with a two-week delay between the start of each batch’s training. CMDs in the control group will provide care as usual, continuing their routine work. They will not receive any PRITAH components (policy, kick-off meeting and training, on-the-job coaching and consultation, and alternatives for involuntary treatment). Moreover, CMDs in the control group are free to address involuntary treatment according to their usual practice in their respective organization. CMDs on maternity leave, long-term sick leave, nearing retirement, or newly recruited during the PRITAH-implementation period are excluded from the study. In a nested design, as part of the effect study, all 88 participating CMDs will report on the use of involuntary treatment by formal and informal caregivers for 10 randomly selected clients within their caseload to provide insights at the client level. If a client drops out of the study due to discontinuation of care (i.e. institutionalization or end of life), they will be replaced by another randomly assigned client from the caseload of the CMD. Therefore, we anticipate collecting 880 responses on client level. See Fig. 1.

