#### Implementation outcomes

Primary outcomes for the PRITAH-implementation include adoption, acceptability, appropriateness, feasibility, fidelity, and sustainability, as defined by Proctor [45–47]. These outcomes are used to capture the initial uptake, practical integration, and long-term embedding of PRITAH within the healthcare organizations and CMDs [48]. The outcomes will be assessed using self-administered questionnaires based on Proctor’s definitions, PRITAH-training observations, PRITAH-training evaluation forms, attendance lists, and focus groups with PRITAH-trainers and managers of the organizations [46]. The questionnaires contain multiple statements for each outcome measure, with responses rated on a 5-point Likert scale ranging from totally disagree to totally agree. The development of the questionnaire is based on the Acceptability of Intervention Measure (AIM), Intervention Appropriateness Measure (IAM), and Feasibility of Intervention Measure (FIM) [45]. Furthermore, both the phrasing and the content of the statements were reviewed by experienced researchers in implementation science to assure face validity. To complement data on the implementation outcomes, additional qualitative data will be collected. During the nine PRITAH-workshop sessions (three training groups with three sessions each), a member of the research team takes observations through field notes to assess whether the trainers adhered to the protocol and whether modifications were made. PRITAH-training evaluation forms, containing both closed and open-ended questions are distributed and completed after each workshop to gather feedback on that specific session. The output of these evaluation forms will be used as input for the two focus group meetings with both PRITAH-trainers and managers from the participating organizations. Lastly, attendance lists are recorded. See Table 2 for a summary of the implementation outcomes and measurements.

**Table 2 Tab2:** Implementation outcomes

Implementation outcome (Proctor, 2011)	Operationalisation description	Measurement	Target group	Timepoint
Adoption	The intention and decision to engage with PRITAH and its four key elements, reflecting how well the intervention is embraced by healthcare professionals	Questionnaire PRITAH-training evaluation forms Focus group meeting	CMD (IG) Trainers Managers	T0, T1

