##### Effect outcomes

Outcomes at the CMD level (attitude, subjective norms, perceived behavioural control, and intention) will be analysed with mixed (multilevel) regression, with linear regression for continuous outcomes and generalized linear regression (e.g., logistic, ordinal, gamma) for categorical outcomes. A total score per CMD or client per time point will be calculated for each outcome measure if multiple items measure the same construct and share the same response format (e.g. all items are binary or all items use a 5-point Likert scale). Repeated outcome measures are nested within CMDs. The fixed (predictor) part of the mixed model will include intervention (yes/no), region, care organization, and time point (t0, t1, t2; week 0/8/20), along with age, gender, educational level, work experience in care for older people, work experience in professional home care, current position, number of working hours, and hours working with individuals with dementia. Additionally, interaction of each predictor with time will be evaluated. The random part of the model will account for unexplained outcome variation between CMDs, which is allowed to change over time, by assuming an unstructured residual covariance matrix (marginal model). Predictor by time interactions will be deleted if not significant, with exception of the key interaction between intervention and time. Giving the nonrandomized treatment assignment, additional analysis will be (a) comparing treated and controls with respect to the baseline outcome measurement, adjusted for all abovementioned confounders, and (b) repeating the above mixed regression, but now with the baseline outcome as covariate instead of as repeated measures. This approach will help assess Lord’s paradox as a sensitivity/robustness analysis [43, 55].

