All participating CMDs will be included into the analyses with all available data without imputing missing outcome measurements using maximum likelihood estimation. This approach is valid under the Missing At Random (MAR) assumption and is asymptotically equivalent to multiple imputation when using an appropriate imputation model [56]. Additionally, outcome missingness will be analyzed as a separate dependent variable using logistic regression (missingness at any given time point: yes/no) or mixed logistic regression for repeated measures (missingness at each time point), depending on the frequency and pattern of missing data. Covariates that predict missingness will be identified and incorporated into the primary outcome analyses.

Outcomes at the client level ((total score on the involuntary treatment questionnaire, and score per subscale (i.e., physical constraint, non-consensual care, the use of psychotropic medication)) will be analyzed in the same way as outcomes at the CMD level, with two modifications. First, predictors at the client level such as the client’s age, gender, living situation, informal caregiver, diagnosis, and presence of professional of homecare will be included as covariates. Second, unexplained outcome variation at the client as well as at the CMD level will be modeled with an unstructured covariance matrix [42].

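### The effect models ignore the three shared training groups in the intervention arm; if outcomes correlate within groups, the standard error of the intervention effect is too small

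*Protocol article*

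**What the plan says.** Delivery is described in three places in the protocol article. Under Sample, intervention CMDs "receive training in batches of 10 to 14 people", "with a two-week delay between the start of each batch’s training". Under Measurements, Implementation outcomes, the nine workshop sessions are broken down as "three training groups with three sessions each". Table 1 adds, on coaching: "The trainers of the workshops will serve as a coach". Controls receive no PRITAH component, so they have no counterpart to these groups.

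The error structure is set out under Data analyses, Effect outcomes. For CMD outcomes, "Repeated outcome measures are nested within CMDs" and "The random part of the model will account for unexplained outcome variation between CMDs", with an unstructured covariance over time. For client outcomes, which include the primary effect outcome, "unexplained outcome variation at the client as well as at the CMD level will be modeled with an unstructured covariance matrix". The fixed part lists intervention, region, care organization, time and CMD characteristics. Neither part contains a training-group or trainer term.

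**The concern.** CMDs who sit through the same workshops share discussions, case studies and the way the material was delivered on the day. T0 is taken before the first workshop, so any likeness that this creates appears at T1 and T2, in the intervention arm only. This is a partially nested design. A model whose highest level is the CMD counts the trained CMDs as that many independent replicates of PRITAH, given region and organization.

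This differs from the geographical grouping used for allocation. Districts and villages exist in both arms, whereas training groups form after allocation in one arm, and a group of 10 to 14 may pool several districts. A district term would not in general absorb a training-group effect.

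At stake is the interval around the intervention effect. One unusually good or poor training group could be read as an effect of PRITAH in general. That matters because the article's abstract and discussion look towards broader implementation and generalizability.

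**Working it through.** The article states no power, effect size or significance level, so there is no figure of its own to reproduce. The session count does agree: 3 groups × 3 sessions = 9.

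**Inputs from the article**
- Three training groups of m = 10 to 14 CMDs, so n1 = 3m = 30 to 42 trained CMDs.
- 88 CMDs in total ("all 88 participating CMDs will report on the use of involuntary treatment"). The split between arms is not stated. If all take part, controls number n0 = 88 − 3m = 58 to 46.

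**Assumptions**
- Training-group ICC ρ, the share of variance in the CMD-level score (or its change) that is due to group: 0.02, 0.05 or 0.10. The documents give none.
- Equal total variance in both arms, equal group sizes, two-sided 5% test.

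**Formulas**
- Variance assumed without a group term, in units of the CMD-level variance: 1/n1 + 1/n0.
- Variance with group correlation in the trained arm: (1 + (m − 1)ρ)/n1 + 1/n0.
- SE ratio R = square root of the second over the first.
- Actual error of the nominal 5% test ≈ 2 × (1 − Φ(1.96/R)).

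**Worked case (m = 12, ρ = 0.05)**
- Without group term: 1/36 + 1/52 = 0.0278 + 0.0192 = 0.0470.
- With group correlation: 1.55/36 + 1/52 = 0.0431 + 0.0192 = 0.0623.
- R = √(0.0623/0.0470) = 1.15. Error = 2 × (1 − Φ(1.96/1.151)) = 0.089.

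**All cases: SE ratio, and error by formula (by simulation, 40,000 runs each)**

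| Groups (trained/control) | ρ = 0.02 | ρ = 0.05 | ρ = 0.10 |
|---|---|---|---|
| 3 × 10 (30/58) | 1.06; 0.064 (0.066) | 1.14; 0.085 (0.084) | 1.26; 0.120 (0.120) |
| 3 × 12 (36/52) | 1.06; 0.065 (0.064) | 1.15; 0.089 (0.088) | 1.29; 0.127 (0.127) |
| 3 × 14 (42/46) | 1.07; 0.066 (0.066) | 1.16; 0.090 (0.091) | 1.30; 0.130 (0.129) |

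At ρ = 0 both methods return about 0.05.

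**Do the organization fixed effects remove it?** No. With groups of 12 and four organizations as fixed effects, simulated error at ρ = 0.05 is 0.088 if groups cut across organizations and 0.087 if each group comes from one. At ρ = 0.10 it is 0.126 and 0.119.

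**Can the group variance be estimated instead?** Hardly. A test that takes the trained-arm error from the three group means, with Satterthwaite degrees of freedom, has only 2 degrees of freedom for that part. At ρ = 0.02 its simulated error is 0.060-0.068, no real gain on 0.064-0.066, and its interval is narrower than the planned one in 37-39% of runs. For an assumed effect of 0.6 SD at the same ρ, power falls from 74-78% to 52-59%. By contrast, inflating the SE at a fixed ρ brings the error back to about 5% when the assumed ρ is right.

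**The case against.** The strongest objection is that the problem is conditional. With no ICC in the documents, a reader might infer that the test does reject too often; the article does not support that as fact. At ρ near zero nothing is wrong, and at 0.02 the excess is small. This stands, and the point is worded accordingly.

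A reader might also infer that each group has its own trainers and coaches. The article says that workshop trainers also coach, but not how trainers are assigned to groups. If one team serves all three, trainer quality adds nothing between groups. Consultation may also take place in team meetings, which need not follow training groups. This stands too; shared sessions alone are enough for the point.

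The sizes are for a generic CMD-level score. The primary effect outcome concerns care given by formal and informal caregivers to ten clients per CMD, so the group share of variance may well be lower there. This also stands.

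It can be said that extra sensitivity analyses belong in an analysis plan. This carries less weight, because the article itself specifies the levels of the random part, the covariance form and the covariates, and training group is in none of them.

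Finally, this is a Hybrid Type 3 study whose implementation outcomes are descriptive, and delivery is observed in all nine sessions. That lowers the stakes, but field notes do not correct the standard error of the effect analysis.

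**Conclusion.** The point holds in conditional form. The intervention arm is trained in three shared groups, the control arm has none, and the stated models stop at the CMD. For any positive training-group ICC the intervention-by-time standard error at T1 and T2 is too small. For ICCs of 0.02, 0.05 and 0.10 the shortfall is moderate, as tabulated: slight at the lowest value, and up to about two and a half times the nominal error rate at the highest.

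Those sizes rest on assumed ICCs, equal group sizes, all 88 CMDs taking part, and a CMD-level score. They are not shown for the client-level outcome. Nor does the working support making the conclusion depend on whether the effect stays significant once a group variance is estimated: with three groups, such a rule would often be triggered by low power alone.

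**What to change.** Keep the planned models as the main analysis and add the following before results are known:

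- A sensitivity analysis of the intervention effects at T1 and T2, with the interval inflated for training-group correlation in the intervention arm only, at fixed ICCs (for example 0.02 and 0.05). With the group sizes stated, multiplying the model's SE by R means a factor of about 1.06-1.07 or 1.14-1.16; recompute R from the actual numbers per group and arm.
- The three group-versus-control differences at T1 and T2, reported descriptively.
- A statement that the planned interval treats trained CMDs as independent and that generalisation beyond these three training groups is limited.

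Do not base any decision on a variance estimated from three groups.

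The cost is a few lines of text, a little programming and a slightly wider sensitivity interval. Attendance lists are already kept and should identify each CMD's group, so no new data or further CMDs are needed.

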**Fig. 1 Fig1:**
[figure not shown]
Study-design

As all available CMDs from the participating care organizations will be invited to participate in the study, a formal sample size calculation will not be performed. A separate sample size calculation for clients is unnecessary. The statistical power of the study primarily depends on the number of CMDs, as the variation in intervention status (yes/no) occurs between CMDs rather than between clients within the same CMD [42–44].

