## Discussion

The current protocol describes the design of a quasi-experimental Hybrid Design Type-3 effectiveness-implementation study. Implementing new healthcare interventions into real-world practices can be challenging and time consuming [57]. Challenges regarding implementation often depends on the context in which the intervention is implemented, the individuals in the process, and the characteristics of the intervention itself [58, 59]. To address these challenges, conducting a context analysis is essential [58, 60]. Therefore, the current protocol was developed based on the results from a prior context analysis for the PRITAH-implementation (*to be submitted*). In two focus groups with policy staff members, a district nurse, CMDs, managers, and directors, we explored barriers and facilitators using the Consolidated Framework for Implementation Research (CFIR) [58, 60]. Overall, the context analysis revealed that both participating home care organizations support the implementation of PRITAH to prevent or reduce involuntary treatment at home.

Although randomized controlled trials (RCTs) are considered the gold standard in research, our study uses a quasi-experimental design. This type of design is more often recognized for their use in implementation studies where strict randomization may be infeasible or unfitting [61]. In our study, communication between CMDs within the same care organisation and region might induce treatment contamination. Hence, stratification based on region and district is necessary.

A Hybrid Type 3 Design is well suited for this study as the success of the PRITAH-intervention is determined both by how well it can be implemented into existing homecare settings and by its effect on client outcomes. Recommended conditions for a Type 3 Design, as outlined by Curran and colleagues, further support his approach The first condition is that, although the full effectiveness of the PRITAH intervention has yet to be established, research has demonstrated sufficient indirect evidence of its effectiveness, warranting further exploration of its implementation. Another supportive condition for this type of design is the legislation on involuntary treatment (Care and Coercion Act) and the in 2024 released guidelines, which creates a good momentum for implementation [35, 62].

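### Whole districts or villages are allocated to condition, but the effect models have no district level, so the intervention-by-time test is too liberal if case managers in a district change together

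*Protocol article*

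**What the plan says.** **Allocation.** The protocol article, Sample section, states that "all CMDs within the same district or village are grouped together, resulting in multiple clusters", and then: "These clusters are then allocated to either the intervention or the control condition". The unit that receives a condition is therefore the district or village. The Discussion gives contamination as the reason and adds that "stratification based on region and district is necessary". The number of clusters is not given.

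**Power.** The paragraph after Fig. 1 makes no formal sample size calculation. It rests power mainly on the number of CMDs because "the variation in intervention status (yes/no) occurs between CMDs rather than between clients within the same CMD".

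**Models.** In Data analyses, Effect outcomes, the CMD-level model nests repeated measures in CMDs. Region and care organization are among its fixed effects, and of the rest it says: "The random part of the model will account for unexplained outcome variation between CMDs". For the client-level outcomes, which include the primary effectiveness outcome, "unexplained outcome variation at the client as well as at the CMD level will be modeled with an unstructured covariance matrix". District or village appears in neither the fixed nor the random part of either model. The two additional analyses (a baseline comparison, and baseline as covariate) do not add it.

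**The concern.** When groups are allocated, the treatment comparison is made between groups. Any correlation among members of a group that the model leaves out goes into the error of the treatment effect but not into its standard error.

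The article gives its own reasons to expect such correlation:
- CMDs are kept together by district because they interact.
- Homecare is organized in small districts, each with one team and a responsible district nurse (Setting).
- The outcome covers involuntary treatment by formal and informal caregivers, not only the CMD's own practice.
- The Discussion expects CMDs to spread the intervention through district teams.

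An effect that spreads through a shared team would tend to move the CMDs of that district together. At stake are the intervention-by-time test and its confidence interval, for the primary effectiveness outcome and for the CMD-level outcomes. The error would favour a false claim of effect.

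**Working it through.** **Inputs from the article.** 88 CMDs; 10 clients per CMD, so 88 × 10 = 880 client responses, which agrees with "we anticipate collecting 880 responses on client level". No power, effect size, SD, ICC or number of districts is stated, so there is no power figure to reproduce.

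**Assumptions.** m = 2 to 9 CMDs per district (about 44 down to 10 districts), and a district ICC of 0.05 to 0.10 for the CMD's change over time, after the planned fixed effects.

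**CMD-level outcomes.** Design effect DE = 1 + (m − 1) × ICC. True SE / model SE = √DE. Effective CMDs = 88 / DE. True two-sided alpha = 2 × [1 − Φ(1.96/√DE)].

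Each cell gives ICC 0.05 / ICC 0.10:

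| m (districts) | DE | SE ratio | Effective CMDs | True alpha |
|---|---|---|---|---|
| 2 (44) | 1.05 / 1.10 | 1.02 / 1.05 | 84 / 80 | 5.6% / 6.2% |
| 4 (22) | 1.15 / 1.30 | 1.07 / 1.14 | 77 / 68 | 6.8% / 8.6% |
| 6 (about 15) | 1.25 / 1.50 | 1.12 / 1.22 | 70 / 59 | 8.0% / 11.0% |
| 8 (11) | 1.35 / 1.70 | 1.16 / 1.30 | 65 / 52 | 9.2% / 13.3% |
| 9 (about 10) | 1.40 / 1.80 | 1.18 / 1.34 | 63 / 49 | 9.8% / 14.4% |

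Worked case, m = 9 and ICC = 0.10: DE = 1 + 8 × 0.10 = 1.80; 88 / 1.80 = 49; 1.96 / √1.80 = 1.461; 2 × [1 − Φ(1.461)] = 0.144.

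**Simulation check.** 20,000 runs per setting, 88 CMD scores in allocated districts, unadjusted t-tests at nominal 5%. Rejection under no effect, for ICC 0.05 / 0.10:
- 22 districts: 7.1% / 8.5%
- 16 districts: 7.5% / 10.2%
- 11 districts: 9.4% / 12.9%

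With ICC 0 the CMD-level test rejects in 5.0% to 5.2%. A test on district means stays at 4.8% to 5.3% throughout.

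**Client-level outcome.** Let r_CMD be the correlation between clients of one CMD, and r_district that between clients of different CMDs in one district. The planned model's variance factor is 1 + 9 × r_CMD. With districts it is 1 + 9 × r_CMD + 10 × (m − 1) × r_district. For m = 4 or 8, r_CMD 0.05 to 0.20 and r_district 0.01 to 0.05, the SE ratio is 1.05 to 1.85 and the true alpha about 6% to 29%. The upper end is extreme, since it sets r_district equal to r_CMD and so leaves no variation specific to the CMD. At m = 4, r_CMD 0.10 and r_district 0.01, the factors are 1.9 and 2.2, the SE ratio is √(2.2/1.9) = 1.08 and alpha is 6.9%.

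**Why the fixed effects do not help enough.** Region and organization terms, with or without time, remove differences between regions and organizations. They leave differences between districts within them.

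**The case against.** The strongest reply is that the inflation is conditional. It needs residual district correlation in change over time, and the article gives no ICC. Region, organization and many CMD covariates, with their time interactions, may shrink that correlation. This stands: a reader might infer that the standard errors are certainly too small, and the article does not establish that.

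Other stronger readings also go too far:
- **That the note on power is wrong.** It contrasts CMDs with clients and says power depends primarily on CMDs. That contrast is correct and supports its purpose, which is to dispense with a client sample size. It only omits the cluster level. No stated power is overturned, since none was calculated.
- **That the effective sample is the number of clusters.** That would hold only at ICC = 1. The number of clusters limits the degrees of freedom; the effective number of CMDs lies between.
- **That CMDs of one district share a training batch.** The article does not say so. Batch correlation would be a separate matter.

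The simulation is an unadjusted t-test with assumed cluster counts, not the planned model, so it shows the mechanism and rough size only.

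One could read stratification by district as placing both arms in each district. The Sample section rules this out, because all CMDs of a district go together. Nor is the gap a detail left for a fuller document: the article lists covariates, nesting, random part and covariance structure, and that stated hierarchy stops one level short.

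**Conclusion.** The mismatch is established by the text: the allocated unit is missing from models that are otherwise specified in detail. Its consequence is conditional. Under the assumed 2 to 9 CMDs per district and ICC of 0.05 to 0.10, the loss runs from trivial (84 effective CMDs, alpha 5.6%) to serious (49 effective CMDs, alpha about 14%). Under an ICC of 0 the planned CMD-level test is valid. The position within this range cannot be settled from the article. The point concerns the effectiveness aim only; the primary implementation outcomes are analysed descriptively. It should be corrected before analysis, because the clusters are already defined by the allocation.

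**What to change.** 1. In both the CMD-level and the client-level model, account for district or village as the allocated unit. One route is a district random effect that includes district-by-time, with small-sample degrees of freedom tied to the number of clusters. A district intercept alone cancels out of the intervention-by-time contrast and would not repair the test. If the full model does not converge, use cluster-robust standard errors with a small-cluster correction, or a cluster-level analysis.
2. Do the same in the baseline-as-covariate analysis. T1 and T2 remain repeated outcomes there, so district effects should be allowed to differ between them.
3. Extend the note on power to say that power also depends on the number of allocated clusters, and report that number per arm.

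Cost: somewhat wider intervals, and possible convergence problems if clusters are few and unstructured matrices are kept at the lower levels. No change to allocation or data collection is needed.
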